## Methods and Analysis

### SPAN Protocol

The QI intervention in the SPAN protocol is outlined in Figure 2 and includes four distinct Tasks:

Assessment: Conduct an assessment of each bridge organization's current implementation, needs, and readiness of AHC Model navigation activitiesPlanning: Engage in a peer planning approach to build capacity for AHC Model navigation activitiesImplementation w/ technical assistance: Co-creation of a QI protocol for AHC Model navigation activitiesEvaluation: Measure the impact of the peer planning and technical assistance (TA) approach.

**Figure 2 F2:**
[figure not shown]
Quality improvement intervention.

Tasks will be replicated with five bridge organizations participating in the national AHC model.

Participating bridge organizations were chosen by an informal assessment of organization implementation needs, and interest in peer technical assistance through conversations between the research team and CMMI program officers. Potential bridge organizations were approached by the research team at the Annual AHC meeting attended by bridge organizations, CMMI and other CMS staff, federal agency partners, and CMS contractors. The research team then worked closely with potential bridge organizations and CMS program officers in follow-up meetings to determine interest and readiness to participate in SPAN. In Task 1, a mixed-method assessment will provide a baseline of the current AHC navigation implementation. Integrated findings from the baseline assessment will guide peer planning to introduce TA resources, to build relational elements and organizational capacity, and to establish priorities and visioning through stakeholder and planning meetings (Task 2). In Task 3, stakeholder meetings will be conducted to develop a quality improvement (QI) protocol and to update current AHC navigation implementation. Alongside the development and implementation of the QI intervention in the SPAN protocol, a mixed method, convergent parallel study will evaluate the impact of the peer planning approach and TA on implementation and navigation outcomes (Task 4). The study design will allow for accurate measurement of selected Consolidated Framework for Implementation Research (CFIR) constructs from Figure 1 while providing a complementary set of data for the overall national AHC Model without harming any desired measures for the larger national AHC evaluation or other outside evaluations. Study results will integrate findings across bridge organizations about AHC activities and navigation outcomes with the evaluation of the multi-level QI intervention and individual QI protocols.

### Task 1 – Assessment of Current Implementation, Needs, and Readiness of AHC Model Navigation Activities

#### Document Review

Through a document review, the current AHC Model activities related to navigation at each bridge organization will be outlined. Documents will include standard operating procedures (SOPs), patient navigation implementation plan, navigation milestone plan, and any other documents relevant to AHC Model implementation. A SOP outlines the steps involved to carry out an implementation specific activity. The purpose of an SOP is to facilitate consistent protocol implementation across CDS and years of the AHC Model implementation as staff members change. SOPs identify the purpose of the activity, owner of an activity, and participants in the activity. The implementation plan walks the reader through the plan for launching the activities required by the AHC Model. This document gives the organizational structure of the AHC Model for each specific bridge organization taking into consideration their CDS. The plan also gives a brief outline of the activities that will be conducted through the course of the AHC Model implementation. The Centers for Medicare & Medicaid Services Innovation Center (CMMI) has set target goals for each bridge organization to reach regarding screening and navigation activities. When the target numbers were changed, bridge organizations were asked to detail how they would alter their activities to meet the new goals. The milestone plan requires that implementation shift to meet the new numbers. The milestone plan will vary by bridge organization as it was up to each bridge organization to decide what course of action, they would take to meet the new numbers.

A keyword analysis will be conducted to develop common codes and themes using NVivo 11 (QSR International) software (42, 43). Relative frequencies and weighted percentages of words will be carried out to determine common codes. Those words with weighted percentages over 1.00%, will be considered for common codes. Using the keyword analysis, similar words will be combined to common codes (e.g., adding managers, teams, etc. to staff). The coding structure will differ by bridge organization and will include any emerging codes. The coding framework will be then used by the research team to code the documents. After the initial coding, the researchers will compare their coding structure and collapse codes into larger key themes. The themes will be considered in terms of their relationships to one another within AHC Model navigation activities and represented through process maps created by the research team.

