## Quality Improvement Approaches

Integrating QI approaches from lean manufacturing into the clinical healthcare space has provided positive and successful results (40). This kind of improvement is deemed “total quality management” and applies both qualitative and quantitative methods to ensure that healthcare processes produce outcomes which achieve desired results (41). *Lean Six Sigma* utilizes a 5-step method to assess if the desired quality of the healthcare outcome is achieved (41). These adapted steps are: define the goals; measure the current process; analyze to verify the relationships and causality of factors; improve the process based on the experimental analysis; and provide control to ensure the variances are corrected (41). This method combines the precision of replicating standards that can be grounded by the scientific method. *Lean Six Sigma* empowers staff with a defined framework for change that can improve work flows and meet identified strategic priorities. Collaboration is the hallmark of this methodology, and because it is process focused it does not interfere with the professional judgment of healthcare practitioners. Management buy-in is extremely important in the maintenance efforts to sustain these changes for the long-term and to empower other site staff and ensure long-term sustainability and success. We will use *Lean Six Sigma* as our QI method for the navigation process. As with traditional *Lean Six Sigma* initiatives, our aim is to improve performance, in our case navigation performance. We differ from the traditional *Lean Six Sigma* practice whereas waste and variation are removed, instead we seek to identify site specific solutions to reach common goals of improved AHC Model implementation and outcomes in the proposed Strengthening Peer AHC Navigation (SPAN) study protocol. The aims of the SPAN study protocol are to implement and evaluate a new multi-level quality improvement (QI) intervention to improve the Accountable Health Communities (AHC) Model implementation and navigation milestones through a structured peer planning and to provide successful technical assistance for the AHC Model.

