In the first stakeholder committee meeting, the research team will review the SPAN protocol and memorandums of understanding (MOUs), roles and responsibilities for committee members will be assigned, a communication plan will be created, and all committee members will agree on the goals for stakeholder meetings. In the second stakeholder meeting, baseline navigation data collection to identify if current navigation milestones are being met by bridge organizations and findings from the assessment (Task 1) will be discussed. The baseline navigation data will be collected from monthly monitoring reports each bridge organization must provide to CMMI. Before the meeting, the research team will present the process maps of the bridge organization's current site activities based on the assessment findings. Bridge organization and CDS stakeholders will review and provide feedback on the process maps during the meeting. During the first planning session meeting, the research team will review and make any additional modifications to the process map(s) created in the stakeholder meeting. Based on the assessment and process mapping, staff will align current implementation strategies with best practices based on the ERIC implementation strategies for multi-component interventions (34). In the second planning session meeting, an IM planning session will be held to focus on areas where QI could be helpful for the AHC site's current implementation approach and focus on prioritization of AHC implementation performance objectives and determinants. The aim of the second planning meeting is to identify between two and four modifiable determinants to be mapped to specific ERIC implementation strategies for QI. The staff will use these strategies to create the QI protocol, revised standard operating procedures (SOPs), implementation plan, navigation milestone plan, and other relevant QI documents at the third and fourth stakeholder meetings.

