### Task 3 – Co-creation of a Quality Improvement (QI) Protocol for AHC Model Navigation Activities

Following peer planning, a third stakeholder meeting will be held with each bridge organization to develop a quality improvement (QI) protocol and to update QI documents for AHC Model implementation at the CDS. The QI protocol allows each bridge organization to demonstrate AHC navigation implementation achievement and determine short term impact on milestones. The protocol will build on activities and data collected in Tasks 1 and 2. The fourth stakeholder meeting will focus on key components of a QI protocol and completion of a written QI protocol. As shown in Table 2, the QI protocol will be completed using the Quality Improvement (QI) Bridge Organization Team Charter Template. The template was adapted from QI protocol charters developed by the Agency for Healthcare Research and Quality (AHRQ) Quality Indicators Toolkit (44), Institute for Healthcare Improvement (IHI) (45), and CMS Medicare Quality Assurance and Performance Improvement programs (46). The purpose of the template is to describe the stakeholder committee roles, QI protocol aims, scope and timeline, protocol implementation strategies, and change management strategies (e.g., how to measure QI protocol success). Upon review and approval by each bridge organization, the protocol will be sent to CMMI for review and approval. CMMI leadership and program officers will review the protocol to ensure there is no overlap with existing Model activities or budgetary fund allocation. Upon approval by CMMI, each bridge organization will complete the Quality Improvement Protocol Readiness Assessment Checklist outlined in Table 3 (47). Upon expressing readiness to implement the QI protocol, bridge organizations staff will be assigned to the new protocol, budgetary funds will be released to support implementation by the bridge organization and implementation will begin. A minimum of two additional stakeholder meetings will be held during QI protocol implementation to provide facilitation, support, and ongoing assistance to each bridge organization.

**Table 2 T2:** Quality improvement bridge organization team charter template.

Bridge Organization Name:
QI Protocol Aim:
Bridge Organization QI Protocol Sponsor:
Protocol Background:
QI Protocol Scope:
QI Protocol Implementation Strategies:
QI Protocol Change Management Strategies (take from planning meetings):
Estimated Date for Start and End of QI Protocol:

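### The within-site comparison of 12 prior months with about 6 QI months cannot separate SPAN from the CMMI-prompted milestone-plan shift if that shift fell within or after a site's baseline

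*Protocol article*

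**What the plan says.** Document Review (Task 1) explains that CMMI "has set target goals for each bridge organization to reach regarding screening and navigation activities". It continues: "When the target numbers were changed, bridge organizations were asked to detail how they would alter their activities to meet the new goals". On the resulting plan it says "The milestone plan requires that implementation shift to meet the new numbers", and that "The milestone plan will vary by bridge organization as it was up to each bridge organization to decide what course of action" to take. No target values, date or direction of change are given.

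Milestones are also part of what SPAN is meant to achieve. The aim under Quality Improvement Approaches is "to improve the Accountable Health Communities (AHC) Model implementation and navigation milestones through a structured peer planning", and Task 3 says: "The QI protocol allows each bridge organization to demonstrate AHC navigation implementation achievement and determine short term impact on milestones".

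Evaluation of the QI Protocols (Task 4) describes the numerical comparison. Each site extracts the preceding 12 months from its monthly monitoring report as baseline, and about 6 months of intervention data are anticipated. The example measures are counts: beneficiaries accepting navigation, core needs resolved, and cases closed without any need met. The two periods are summarised and compared by a parametric or non-parametric method. No comparison site is mentioned, and nothing ties the baseline to the target change.

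Task 2 lists the navigation milestone plan among the documents that staff produce with the strategies chosen under SPAN.

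**The concern.** The article itself identifies a change in site activity that began outside SPAN, differs by site and is aimed at the same navigation activities SPAN seeks to improve. It then defines the baseline purely by the calendar, whatever targets or milestone-plan activities were in force during those 12 months.

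In an uncontrolled before-after comparison, a change in activity that starts part-way through the baseline, or later, enters the difference between periods. A rise in counts would be credited to peer planning and technical assistance, and a fall would be held against them. The error would carry upward, because Evaluation of the QI Intervention uses the QI-protocol outcomes as measures of success for the whole intervention. The Discussion counts the ability to evaluate the impact of technical assistance as a strength and does not mention this co-intervention.

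**Working it through.** The article states no sample size, power, alpha or effect size, so there is no figure to reproduce. The check asks how much of an outside shift would appear as a SPAN effect, depending on when it starts.

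**Inputs from the article:** 12 baseline months, about 6 intervention months, within-site comparison of counts.

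**Assumed, for illustration only:** true SPAN effect zero; a step shift of relative size s (10%, 20% or 30%) that begins after k baseline months and then persists.

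**Apparent change.** With underlying mean m:

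- baseline mean = m × [1 + s(12 − k)/12]
- QI-period mean = m × (1 + s)
- apparent change = (1 + s) / [1 + s(12 − k)/12] − 1

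For s = 20%:

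- complete before baseline (k = 0): 1.20/1.20 − 1 = 0%
- starts in month 7 (k = 6): 1.20/1.10 − 1 = 9.1%
- starts in month 10 (k = 9): 1.20/1.05 − 1 = 14.3%
- starts with the QI period (k = 12): 1.20/1.00 − 1 = 20%

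The sign follows the shift. A 20% fall from month 10 gives 0.80/0.95 − 1 = −15.8%.

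**Chance of a significant increase with no SPAN effect.** Further assumptions: one site, monthly mean 50, SD 20% of the mean, independent normal months, Welch t-test at two-sided 0.05 (so 2.5% nominal in the upward direction), 20,000 simulations.

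| Shift starts | Apparent gain, s = 10 / 20 / 30% | Chance of significant increase, s = 10 / 20 / 30% |
|---|---|---|
| Complete before baseline | 0 / 0 / 0% | 2.6 / 2.4 / 2.4% |
| Baseline month 7 | 4.8 / 9.1 / 13.0% | 6.5 / 11.3 / 17.2% |
| Baseline month 10 | 7.3 / 14.3 / 20.9% | 9.2 / 20.3 / 34.8% |
| Start of QI period | 10 / 20 / 30% | 13.4 / 34.6 / 58.7% |

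With no shift at all the chance was 2.5 to 2.7%. Timing therefore decides whether there is a problem, and timing is what the article does not give.

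**Precision cost of a shorter baseline.** With b usable baseline months and monthly SD σ, the standard error of the difference in means is σ × √(1/b + 1/6):

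- b = 12: 0.500σ
- b = 6: 0.577σ, which is 15% larger (0.577/0.500 = 1.155)
- b = 3: 0.707σ, which is 41% larger (0.707/0.500 = 1.414)

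**The case against.** A reader might infer that a site could pass from missing its milestone to meeting it merely because the target moved. The documents do not support that as a flaw in the planned analysis. Task 4 gives counts as its examples, and a changed target does not alter a count. Met or missed status appears only in Task 2, as "baseline navigation data collection to identify if current navigation milestones are being met by bridge organizations", for discussion at the second stakeholder meeting. Task 3 does not define impact on milestones as crossing a threshold. The direction is also unknown: if targets rose, meeting them became harder. Only the change in activity can bias the counts.

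The timing may remove the problem too. The target change is described in the past tense, and the milestone plan is an existing document reviewed in Task 1. If the shift was complete before the baseline, nothing is biased. This stands, and the point is conditional for that reason.

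There are partial safeguards. CMMI checks each QI protocol for overlap with existing Model activities. Process maps record activities before the QI protocol is written. Evaluators not directly involved in delivering the QI intervention compare planned with current activities. External policy and incentives are discussed as a possible moderator, and moderators guide the interviews. These help to describe what changed and why, but none removes an outside shift from the counts.

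Finally, this can be called the ordinary history limitation of a before-after study, with details left to a fuller protocol or analysis plan that is not shown. That is fair for the choice of test. It is less so here, because the article names the specific co-intervention and also states the baseline rule that ignores it.

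**Conclusion.** The point holds conditionally and should be acted on. If a site's milestone-plan shift began within its 12-month baseline or later, the planned comparison attributes some or all of the resulting change in counts to SPAN. If it was complete before the baseline, this bias is absent.

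For an assumed 20% rise the spurious gain runs from 0% to 20%, and the chance of a falsely significant increase from about 2.4% to 34.6%. These figures rest on an assumed step change, independent months and an assumed test. They show how the result depends on timing and do not estimate what happened at any of the five sites.

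Two stronger readings should be avoided. The documents do not show that a moved target alone creates an apparent effect. Nor do they support treating all milestone-plan activity as external to SPAN, because Task 2 makes that plan one of the documents produced under SPAN.

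**What to change.** - From the Task 1 document review, record for each site the date of the target change and the date its milestone plan was launched.
- Start the baseline after the launch, or split it at that date, and show monthly counts for the whole period with the break marked.
- If milestone attainment is reported, score both periods against the same target.
- In the fidelity review, distinguish milestone-plan activities adopted before SPAN from those created or revised under SPAN. The latter belong to the intervention.

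The cost is protocol wording and two dates per site from documents already being reviewed. The downside is fewer usable baseline months where the change fell inside the 12, with the loss of precision shown above. Where the launch coincides with or follows the start of the QI period, no post-launch baseline exists, and the report should say that the two influences cannot be separated at that site. If the shift built up gradually, starting the baseline at launch reduces the bias but may not remove it, which is a further reason to show the monthly series.

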#### Semi-structured Interviews

The second part of the assessment includes semi-structured interviews with staff and patients involved in AHC Model navigation. Semi-structured interviews with staff will assess perceptions of AHC Model activities, coupled with individual and organizational needs and readiness related to changes in AHC navigation. Semi-structured interviews with patients will assess perceptions and the impact of AHC navigation implementation on their social needs and quality of life. The interviews will expand on the findings from the document review, expanding the understanding of AHC activities and possible moderators to AHC navigation implementation success. Moderators for implementation success identified in Figure 1 will guide the interview questions to address the protocol aims surrounding AHC Model activities and the AHC navigation implementation. Interview guides are available in the Supplementary Material. Interviews will be conducted over videoconference (i.e., WebEx) or phone and verbal consent will be obtained before the start of the interview. We expect to interview at least three staff members and at least five patients from each bridge organization. Staff members will be contacted by email. During routine navigation interactions over the phone, navigation staff will pre-consent 15 patients to be contacted for an interview by the researchers. During the pre-consent, patients will be given the name and contact information of the research team member coordinating the interviews. If consent is obtained, navigation staff will capture patient contact information and a randomly generated number (ID) will be assigned. Once consent from 15 patients has been obtained, navigation staff will provide patient information to the researchers through a password-protected, cloud file approved for the storage of Health Insurance Portability and Accountability Act (HIPAA) information. Patients will be contacted within 2 weeks of pre-consent by phone or email. A standardized pre-consent process and interview recruitment and introduction script will be created. If the patient is not reached after three attempts during the first 2 weeks, attempts to contact that patient will cease.

Interviews will be audio-recorded, transcribed verbatim, and analyzed thematically using NVivo 11 (QSR International). Transcripts will be checked for accuracy through readings and listening to transcripts. Based on the CFIR framework, the research team will create a coding structure for staff interviews and utilize a similar framework but modified for patient interviews. The coding frameworks will then be used by multiple research team members to code each transcript. Codes can be revised, added, and removed throughout the team coding process. The research team members will meet to review individual coding, identify patterns identified with codes, and develop common themes. Interview themes will be used to update the process maps to better reflect navigation activities, as needed. While interviews themes will be identified in each bridge organization assessment, study findings will be described more broadly across bridge organizations.

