#### Evaluation of the QI Protocols

The evaluation of the QI protocols will be completed by the research team in collaboration with the staff implementing the QI protocol at each bridge organization and the CDS. The staff implementing the QI protocol will evaluate their own protocol in order to provide the staff with the tools and skills needed to conduct and assess future QI protocols (capacity building). Implementation fidelity will be assessed using similar metrics and methods as described for the QI intervention evaluation (see above description). During the planning process for the QI protocol, the research team staff will work with each organization to identify specific outcomes they want to focus on through their QI protocol. The QI protocols identified during this planning phase will be used to inform the data collected for both the process and outcome evaluation. Outcome measures will be based on data generated from weekly data files submitted to CMMI by each bridge organization as required per the Model terms and conditions of award. Weekly files are converted to CMS records and available through the bridge organization monthly monitoring report in the AHC Portal. We anticipate a period of 6 months of intervention data will be available for each site for comparative purposes. Each bridge organization will extract data from their monthly monitoring report for the previous 12 months, which will serve as the baseline data period. Data extracted for each bridge organization will vary per site and protocol based on the staff identified QI protocol and patient interviews but examples include: the unique number of beneficiaries who accepted navigation, the number of core needs resolved from navigation cases, and the number of closed navigation cases with no core needs met. Data for the intervention period (implementation of the QI protocol) will be extracted using the same report and measures. Descriptive statistics [mean, median, range, interquartile range (IQR)] will be calculated for each time period for all measures and compared across time using parametric or non-parametric statistics as appropriate.

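### Interview patients are recruited only by navigation staff during live navigation calls, with no stated selection rule, so lost and closed cases are left out or under-represented

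*Protocol article*

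**What the plan says.** All references are to the protocol article. The recruitment of patients is described under Task 1, Semi-structured Interviews: "During routine navigation interactions over the phone, navigation staff will pre-consent 15 patients to be contacted for an interview by the researchers". The expected yield is "We expect to interview at least three staff members and at least five patients from each bridge organization", and the SPAN Protocol section adds that "Tasks will be replicated with five bridge organizations participating in the national AHC model". After a patient agrees, "a randomly generated number (ID) will be assigned". On standardisation the text promises that "A standardized pre-consent process and interview recruitment and introduction script will be created". On follow-up by the researchers it says "If the patient is not reached after three attempts during the first 2 weeks, attempts to contact that patient will cease".

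The stated purpose is evaluative: "Semi-structured interviews with patients will assess perceptions and the impact of AHC navigation implementation on their social needs and quality of life". The same section has the interview themes update the process maps. The SPAN Protocol section has the integrated baseline findings guide peer planning. Evaluation of the QI Protocols says that the data extracted at each site depend on the QI protocol identified by staff and on the patient interviews. One of its example measures is "the number of closed navigation cases with no core needs met".

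**The concern.** Two features of the recruitment route work in the same direction. First, entry runs through the navigators, whose work the patients are asked about, and nothing stated limits their discretion over whom to ask. Second, the place of recruitment is a live navigation call. Someone who stopped answering, or whose case has already been closed, is not on such a call.

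Those are people likely to know why navigation does not work for some beneficiaries. The example measures include cases closed without any need met, so the study itself treats that group as important. If the interviews hear mostly from engaged patients, barriers may be under-described and the impact of navigation may look better than it is. That picture would then be carried into the process maps, into the planning session that selects two to four determinants, and into the choice of measures for the site.

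**Working it through.** The plan gives no precision or sample-size figure for this component, so the check is a reading of the text with some counting.

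**Counts.** The sentence on 15 patients does not say per site. At least five interviews at each of five sites is 5 × 5 = 25, which is more than 15, so 15 cannot be the study total; the per-site reading is the consistent one. On that reading, up to 15 × 5 = 75 patients are pre-consented and at least 25 are interviewed, or 5/15 = 33% of those pre-consented at a site. All of them pass through navigation staff.

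**Is there a selection rule?** None is stated. The only random element is the ID number, which is assigned after consent and so does not select anyone. The standardised pre-consent process is still to be written and its content is not given.

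**Who can enter?** Comparing the recruitment setting with case status:

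| Case status | On a routine navigation call? |
|---|---|
| Active, needs being resolved | Yes |
| Active, needs unresolved | Yes |
| Being closed without a need met, if spoken to at closure | Possibly |
| Already closed, with or without a need met | No route described |
| Lost to contact | No route described |
| Declined navigation | No evident route; arguably outside the target group |

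The limit on contact attempts then removes further patients who are hard to reach.

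**Is there other direct patient input?** Task 2 lists research, bridge organization and clinical site staff and other key partners as meeting participants; patients are not named. The interviews under Evaluation of the QI Intervention are with staff. The Study Conceptual Framework nevertheless describes the multi-level approach as including input from patients. The Task 1 interviews are the only place described where that input is collected directly.

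**Where do the findings go?** Into the process maps (Semi-structured Interviews), into planning (SPAN Protocol and Task 2) and into the choice of extracted data (Evaluation of the QI Protocols).

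**Does the article recognise these risks elsewhere?** In part. The QI intervention is to be evaluated by people not directly involved in delivering it, and the Discussion concedes that sites were chosen informally and subjectively. Neither statement is extended to the selection of patients.

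**The case against.** The case on the other side has several parts, and much of it stands.

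- *A reader might infer that patients whom navigation failed cannot be interviewed at all.* The text does not support that. Nothing restricts recruitment to successful cases. A patient still in contact with unmet needs can be asked, and so can one spoken to as the case closes.
- *A reader might infer that navigators pick favourable patients.* The text is silent on selection. The process still to be created could require consecutive approach, and an article may leave call order to a fuller document. This stands, but an order of approach applied to routine calls cannot bring in people who are no longer called. The setting is stated in the article, so it is not an omitted detail.
- *People who declined navigation are arguably outside the target group.* The section concerns patients involved in navigation and asks about its impact on them. This stands, so including decliners is optional.
- *Outcome data do not come from the interviews.* They come from files submitted to the funder and the monthly monitoring reports, which can count failed cases at baseline whoever is interviewed. Document review and staff interviews also feed the assessment. This stands and limits the consequence. Counts do not explain why cases fail, though, and documents and staff give the organization's view.
- *A reader might want a bias in percentage points.* That would need assumed benefit rates for engaged and disengaged patients. It would also describe a proportion that the study never estimates, since the interviews are analysed by theme.

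**Conclusion.** The point holds as a weakness of the recruitment frame in the patient interviews. Staff delivering the assessed service control entry without a stated rule, and patients lost to contact or already closed out have no described way in. The affected material is all the direct patient input described: at least 25 interviews if each of the five sites meets its minimum.

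The expected direction is towards engaged patients. The size of any effect on conclusions cannot be given. The judgement assumes that 15 is a per-site number, that routine calls are mainly to open cases, and that no other patient input is collected. The article does not show that any site's QI protocol would be misdirected, because monitoring data, documents and staff interviews also shape it. This is a worthwhile, cheap improvement to one qualitative component and does not undermine the evaluation as a whole.

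**What to change.** 1. Have the research team set the order of approach: a consecutive or randomly ordered list from each site's navigation records of recent months. Navigation staff may still make the calls, using the planned script, but in that order.
2. Reserve some of the 15 pre-consent slots at each site for recently closed cases with no core need met and for patients lost to follow-up. People who declined navigation may be added if the team wants their view.
3. Log numbers approached, refused, not reached and interviewed, by case status, and report them with the themes.
4. State any remaining under-representation as a limitation, next to the existing one on site selection.

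The cost is drawing up the list, some calls outside routine interactions, and a lower pre-consent yield in the reserved groups. Some lost patients will stay unreachable, which is why the log matters. No additional interviews are needed. With as few as five interviews at a site, the aim is a wider range of experience; comparison between case-status groups would not be supportable.
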